**Methods:**

This trial will be conducted in 12 clinics in Nampula Province, Northern Mozambique. All clinics will implement an optimized standard of care (control) including (1) billboards/posters and radio shows, (2) healthcare worker (HCW) training, (3) one-stop adolescent and youth-friendly services, (4) information/motivation walls, (5) pill containers, and (6) tools to be used by HCW during clinical visits. The CombinADO strategy (intervention) will be superadded to control conditions at 6 randomly selected clinics. It will include five additional components: (1) peer support, (2) informational/motivational video, (3) support groups for AYAHIV caregivers, (4) AYAHIV support groups, and (5) mental health screening and linkage to adolescent-focused mental health support. The study conditions will be in place for 12 months; all AYAHIV (ages 10–24 years, on ART) seeking care in the participating sites will be exposed to either the control or intervention condition based on the clinic they attend. The primary outcome is VS (viral load < 50 copies/mL) at 12 months among AYAHIV attending participating clinics. Secondary outcomes include ART adherence (self-reported and TDF levels) and retention in care (engagement in the preceding 90 days). Uptake, feasibility, acceptability, and fidelity of the CombinADO strategy during implementation will be measured. Trial outcomes will be assessed in AYAHIV, caregivers, healthcare workers, and key informants. Statistical analyses will be conducted and reported in line with CONSORT guidelines for cRCTs.

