### Randomization and blinding

Randomization will be balanced 1:1, with an equal number of study sites randomized to each arm.

A randomization list will be prepared by the independent statistician and passed to the study team. The intervention allocation is open to the study team and will not be blinded to investigators or HCWs and AYAHIV participating in the trial. However, all staff involved in data analysis will be blinded to arm allocation, including the trial statistician. To facilitate this, we will maintain separate databases for variables collected only at intervention sites (including process evaluation measures), independent from data on primary and secondary outcomes collected at intervention and control sites in an identical manner. In addition, laboratory staff involved in measuring the primary outcome will also be blinded to arm allocation.

The independent statistician will maintain randomization codes, and unblinding of the analysis team will occur only after final results using dummy randomization allocation have been completed by the study statistician. As the study team is unblinded to allocation, they will be able to address any issues related to adverse events. If the trial statistician or other personnel working in data analysis become unblinded prematurely for any reason, the principal investigator (PI) and investigator team will be notified immediately. Potential biases introduced through inadvertent unblinding will be examined, along with strategies to mitigate the impact of this on trial reporting.

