#### Statistical analysis

Descriptive statistics will be presented with frequency (percent) or median (interquartile range) depending on the type and will provide overall and by allocation arm. Review of data distributions will be undertaken prior to applying any inferential statistics requiring specific assumptions and methods revised or corrective procedures undertaken. Covariates and specific details of analysis will be fully specified before database closure in a detailed SAP developed by the study statistician and study team. All statistical tests will be two-sided with nominal *α* = 0.05. Study endpoints are binary and will be approached in a similar way. The primary outcome analysis will compare AYAHIV virologic suppression at 12 months post-intervention implementation in intervention versus control sites using generalized estimating equations under a binomial model, with a log link and robust standard errors, providing unbiased marginal estimates of the intervention effect while adjusting for within-cluster correlations. Clustering will be by site using an exchangeable correlation structure. Estimates will be reported as risk ratios (RR) with robust 95% confidence intervals and *p*-values assessed at *α* = 0.05 for all comparisons. No additional adjustment variables will be included in the primary analysis. In subsidiary analyses, we will include covariate adjustment based on confounders selected a priori using direct acyclic graphs. Sensitivity analysis will address potential heterogeneity in clustering by evaluating endpoint models under different assumed correlation structures. Missing outcome data will be handled by complete case analysis in the first case and then by sensitivity analysis substituting alternate outcome values for missing data. Missing data in covariates will be handled by multiple imputations using chained equations. Analysis of secondary endpoints is not conditional on the outcome of the primary endpoint. Secondary endpoints will be approached identically as the primary endpoint. Planned subgroup analyses, which include by age group [10–14, 15–19, 20–24], sex, pregnancy status during the intervention period among females, duration of prior ART use, and ART regimen, will be carried out for primary and secondary outcomes using the same approach as the previously described. Exploratory analyses will include:

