### Sample size and power

#### Primary outcome

The primary outcome analysis will compare AYAHIV virologic suppression at 12 months post-intervention, between intervention versus control sites using generalized estimating equations with robust standard errors, providing unbiased marginal estimates of the intervention effect while adjusting for within-cluster correlations.

For the primary outcome, sample size estimates are based on the following assumptions: 2-sided superiority test with 90% power at *α* = 0.05, clinic sizes of 220 AYAHIV in active care per clinic (range, 113–590), levels of viral suppression < 50 copies/mL of 65% in control clinics (current data estimates this proportion at 48–68%), *ICC* = 0.05 (range, 0.04–0.08). Thus, we estimate that 12 clusters sampling at least 100 AYAHIV each on average will provide > 80% power to detect an absolute increase of 16% in virologic suppression in the intervention versus control clinics.

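### The primary GEE analysis uses robust standard errors on 12 clinics with no small-sample correction or reference distribution named; run in the usual default way, its 5% test has a true type I error of about 9 to 10.5%

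*Protocol article*

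**What the plan says.** The Statistical analysis section fixes most of the primary analysis. Suppression at 12 months is compared "using generalized estimating equations under a binomial model, with a log link and robust standard errors, providing unbiased marginal estimates of the intervention effect". On correlation: "Clustering will be by site using an exchangeable correlation structure". On reporting: "Estimates will be reported as risk ratios (RR) with robust 95% confidence intervals", with p-values assessed at 0.05. On covariates: "No additional adjustment variables will be included in the primary analysis". Secondary endpoints are to be handled identically, and the planned subgroups by the same approach. The Sample size and power section repeats "generalized estimating equations with robust standard errors".

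The abstract gives 12 clinics. Under Randomization and blinding: "Randomization will be balanced 1:1, with an equal number of study sites randomized to each arm", which makes six per arm.

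The article names no bias-corrected variance, no t or F reference, no permutation test and no clinic-level analysis. Its sensitivity analysis changes the assumed correlation structure. A mixed model appears only as an exploratory analysis, in case of heterogeneity between sites. Covariates and specific details are deferred to a SAP, which is not shown.

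**The concern.** The sandwich variance becomes accurate as the number of clusters grows. Recruiting more young people per clinic does not help. With six clinics per arm it is too small on average, and it is itself estimated with only about 10 degrees of freedom. A normal reference ignores that second source of error. Both faults push towards small p-values and narrow intervals.

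At stake is the error rate of the primary claim. A strategy with no effect would reach significance about one time in ten instead of one in twenty, in a trial whose positive result is meant to support scale-up. The endpoints affected are the binary between-arm comparisons: viral suppression, self-reported adherence and retention, with their subgroups.

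**Working it through.** **Inputs from the protocol article.** 12 clinics, k = 6 per arm; arm is the only term in the model, so 12 − 2 = 10 between-clinic degrees of freedom; at least 100 sampled per clinic on average, at most 200; control suppression 65% (48–68%); rise of 16 points, so 81%; intracluster correlation (ICC) 0.05 (0.04–0.08); two-sided α = 0.05.

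**1. The plan's own figure.** For type I error the article gives only the nominal 0.05. The design figure that can be recomputed is power above 80%.
- Design effect: 1 + 99 × 0.05 = 5.95. Effective size per arm: 600 / 5.95 = 100.8.
- Unpooled SE: √[(0.65×0.35 + 0.81×0.19)/100.8] = 0.0615. Pooled SE at 0.73: √[2×0.73×0.27/100.8] = 0.0625.
- Power: Φ[(0.16 − 1.96×0.0625)/0.0615] = Φ(0.61) ≈ 73%.

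With 200 per clinic it is 76.4%. With 100 per clinic and ICC 0.04 it is 80.4%. So the stated power is not reproduced at ICC 0.05, even before any small-sample correction.

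**2. Size of the variance error.** With equal clinics and arm as the only term, the fitted arm mean is the average p̄ of the six clinic proportions pᵢ. The uncorrected sandwich variance of the log risk ratio is the sum over the two arms of Σ(pᵢ − p̄)² / (k² p̄²). An unbiased version divides by k(k − 1) instead of k². The ratio is (k − 1)/k = 5/6. This closed-form SE agreed with a packaged GEE routine (statsmodels) to about 10⁻¹⁴.

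**3. True size of a nominal 5% test, closed form.**
- Uncorrected variance, normal reference: P(|t₁₀| > 1.96 × √(5/6)) = P(|t₁₀| > 1.789) = 10.4%.
- Uncorrected variance, t₁₀ reference: P(|t₁₀| > 2.228 × √(5/6)) = P(|t₁₀| > 2.034) = 6.9%.
- k/(k − 1) correction, normal reference: P(|t₁₀| > 1.96) = 7.8%.
- k/(k − 1) correction, t₁₀ reference: 5% by construction.

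**4. Simulation under no effect** (beta-binomial clinics, 10,000 trials per scenario).

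| Scenario, uncorrected variance and normal reference | Type I error |
|---|---|
| 65% suppression, 100 per clinic, ICC 0.04–0.08 | 9.4–9.9% |
| 65%, 200 per clinic | 9.1–10.4% |
| 65%, clinic samples from 60 to 200 | 9.7–10.6% |
| 48% suppression | 10.4% |
| 81% suppression | 9.4% |

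Coverage of the nominal 95% interval was 89–91%. A run of 40,000 trials per scenario (65%, 100 or 200 per clinic, ICC 0.04–0.08) gave 9.5–10.3%. A 1,500-trial run through the packaged routine gave 8.4%. Its Monte Carlo SE is about 0.7 points, so it is low but compatible with the larger runs.

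Other choices at 65% suppression:

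| Test | Type I error |
|---|---|
| Uncorrected variance with t₁₀ | 6.1–6.9% |
| Mancl-DeRouen variance with normal reference | 4.9–5.7% |
| Kauermann-Carroll variance with t₁₀ | 4.4–4.9% |
| Clinic-level t-test | 4.8–5.2% |
| Mancl-DeRouen variance with t₁₀ | 3.0–3.5% |

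**5. What a valid test costs.**
- Interval width: (2.228/1.96) × √(6/5) = 1.245, about 25% wider.
- Power, 100 per clinic, ICC 0.05: ln(0.81/0.65) = 0.220; SE = √[(0.35/0.65 + 0.19/0.81)/100.8] = 0.0876; ratio 2.51; noncentral t₁₀ power ≈ 62%. Simulation gives 62–63% for the corrected GEE test and 65% for the clinic-level t-test.
- Power, 200 per clinic: effective size 1200/10.95 = 109.6; SE 0.0840; ratio 2.62; power ≈ 66%.
- The uncorrected test shows 77% at 100 per clinic, but part of that is its excess type I error.

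**The case against.** The strongest reply is that this argues from silence. The article says robust; it does not say uncorrected, and it does not name a normal reference. Kauermann-Carroll and Mancl-DeRouen variances are also robust variances, so a valid choice would fit the existing wording. The degrees of freedom and the correction are details that a SAP often supplies, and this SAP is not shown.

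Much of that stands. A reader might infer that the protocol commits the trial to a 10% error rate. It does not: the wording allows tests with true size from about 5% to about 10%, and the upper figure needs both default choices. But the article does not leave the method of inference open. It settles the estimator, link, correlation structure, type of standard error, type of interval and α, then stops short of the one element that decides validity with 12 clusters.

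The other provisions do not repair this. With equal clinic sizes and an arm-only model, changing the working correlation leaves the estimate and its sandwich SE unchanged. The mixed model is exploratory and conditional. The provision for revising methods after looking at the data concerns distributions, whereas the number of clinics is known now.

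A reader might also extend the point to every secondary outcome. The documents do not support that: acceptability and feasibility are assessed qualitatively, and fidelity, cost-effectiveness and the case-control drug-level substudy are not two-arm clinic comparisons of the kind checked here. Nor does the point impugn the risk ratio estimate; the problem lies in the variance and the test.

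**Conclusion.** The point holds conditionally. Under the usual default (uncorrected sandwich, normal reference) the nominal 5% test has a true size of about 9 to 10.5%, and the 95% interval covers about 89 to 91%. With a t₁₀ reference alone the size is about 6 to 7%. The result is stable over the article's ranges for ICC, sample per clinic and control suppression. It assumes beta-binomial variation between clinics, and the closed form also assumes equal clinic samples. It covers viral suppression, self-reported adherence, retention and their subgroups. If the SAP already names a valid correction and reference, what remains is to state them in the protocol and restate the power.

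**What to change.** Before the analysts are unblinded, specify for the primary test: GEE as planned, a bias-corrected sandwich variance (for example Kauermann-Carroll), and a t reference on 10 degrees of freedom for both p-value and interval. Name one check: an unweighted t-test on clinic-level proportions, or a permutation test over the C(12,6) = 924 possible allocations. Apply the same rule to self-reported adherence, retention and their subgroups.

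This takes a sentence or two and a software option, with no new data. The statistical price is real and should be stated: intervals about 25% wider, and power for 65% against 81% at ICC 0.05 of about 63% (100 per clinic) to 66% (200 per clinic). The Sample size and power section should restate its figure for the test that will actually be used.

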Survey questionnaire	o Basic demographic information, education, and vocation information o HIV, STI, ART, reproductive health beliefs and literacy o Adherence and adherence self-efficacy o Youth readiness for independent health care o Relationship/marital status o Mental health o Life events o Substance use o Sexual risk o Reproductive health, including pregnancy and parenthood o Interpersonal violence o Partner, family, and social support o HIV stigma/disclosure o Experience with COVID-19 o Uptake of CombinADO strategy intervention components o Feasibility, acceptability, and appropriateness of all strategy intervention components	AYAHIV	T3
Exit interviews	o Experiences and satisfaction with the services received and various intervention components	AYAHIV	T2
Semi-structured interviews	o Perceived benefits and challenges of attending the support groups o Comfort taking part in the support group o Satisfaction with current support groups structure o Recommendations for refining the existing support groups	Caregivers	T2
	o Experience implementing the intervention, including time spent providing care to AYAHIV o Impact of the intervention on facility and delivery of health services o Met and unmet needs of the AYAHIV population seeking services o Adoption, implementation, maintenance, reach, feasibility, acceptability appropriateness, and fidelity of the intervention various components	HCWs and KIs	T1–T3
Costing questionnaire	o The daily schedule at the health facility o Time spent working across various clinic activities, including consultations with AYAHIV	HCWs	T1 and T2
Blood sampling	o Blood for real-time viral testing o Dried blood spot (DBS) samples for TDF-DP drug-level testing	AYAHIV	T3
Abstraction of AYAHIV routine data	o Date of HIV diagnosis o ART start date o Current ART regimen o Intercurrent hospitalizations o Most recent HIV RNA viral load and CD4 results o Pharmacy dispensing and refill information o Most recent visit date o Retention in care	Clinic records	T3

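### Planned subgroup analyses reuse an arm-contrast model that does not test whether effects differ, and one subgroup (pregnancy) is formed after allocation

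*Protocol article*

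**What the plan says.** The Statistical analysis section of the protocol article names five subgroup factors: age in three bands, sex, and "pregnancy status during the intervention period among females, duration of prior ART use, and ART regimen". The analyses "will be carried out for primary and secondary outcomes using the same approach as the previously described". What precedes that sentence is a binomial GEE with log link that compares intervention with control, clustered by site with exchangeable correlation and robust standard errors. On model terms it says: "No additional adjustment variables will be included in the primary analysis". Covariate-adjusted models appear only as subsidiary analyses aimed at confounding. On testing it says "All statistical tests will be two-sided with nominal" alpha of 0.05, and p-values are assessed at that level "for all comparisons". No arm-by-subgroup term is mentioned. The section also states: "Covariates and specific details of analysis will be fully specified before database closure in a detailed SAP".

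Table 5 (Data collection) lists "Current ART regimen" among the items abstracted from clinic records at T3, the post-intervention time point. The same row lists the ART start date and pharmacy dispensing records. Table 2 shows no pre-intervention assessment of the young people themselves. In Table 5, pregnancy appears only among the topics of the T3 questionnaire.

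**The concern.** Two things are at issue.

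- **The question the model answers.** A subgroup analysis is normally read for whether the effect differs between groups. An arm contrast reported group by group, each with its own p-value, does not address that. If one group falls below 0.05 and another does not, readers tend to infer a difference even when the true effects are equal.
- **When the groups are formed.** Randomisation makes the arms comparable within groups defined by characteristics that allocation cannot alter. Pregnancy dated to the intervention period arises while clinics are already delivering their assigned condition. Regimen recorded at T3 would have the same weakness. If the intervention changes who belongs to such a group, the arms within it are no longer comparable.

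The Discussion says that positive results would support scale-up, so a misleading subgroup statement could affect advice on whom the strategy helps. The primary result is not affected.

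**Working it through.** **1. What the stated model estimates.** The described model is log P(suppressed) = b0 + b1·arm, so exp(b1) is the risk ratio. Applied to subgroups, it gives RR₁, RR₂ and so on. Whether effects differ is a question about RR₁/RR₂. That equals exp(b3) in log P = b0 + b1·arm + b2·G + b3·(arm × G), fitted to everyone. The described model has no b3.

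**2. Timing of the grouping variables.**

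| Factor | Timing in the article | Can allocation affect it? |
|---|---|---|
| Age, sex | No date needed | No |
| Pregnancy | Intervention period, by definition | In principle |
| ART regimen | Undated; only listed item is current regimen at T3 | In principle, if T3 is used |
| Prior ART duration | Undated; ART start date is abstracted | Avoidable by dating it to the start |

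**3. How often equal effects look unequal.** The protocol gives no subgroup figure to reproduce. The nearest is its overall power of more than 80%. With a design effect of 1 + 99 × 0.05 = 5.95 and an effective size of 600/5.95 = 100.8 per arm, the two-proportion formula gives 72.9% (80.4% at ICC 0.04). That discrepancy is a separate matter, and nothing here depends on it.

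Inputs from Sample size and power and from Randomization and blinding: 65% against 65 + 16 = 81%, six clinics per arm, 100 per clinic, ICC 0.05. Assumed: a 50/50 sex split and three equal age groups.

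Power within one stratum, by the same formula:
- Half stratum: m = 50, design effect 1 + 49 × 0.05 = 3.45, effective size 300/3.45 = 87 per arm, power 66.4%.
- One-third stratum: m = 33.3, design effect 2.62, effective size 200/2.62 = 76 per arm, power 60.7%.

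If strata were independent, two halves would disagree on significance with probability 2 × 0.664 × 0.336 = 0.446. Three thirds would not all agree with probability 1 − 0.607³ − 0.393³ ≈ 0.715. Strata in the same clinic share that clinic's effect, so these figures are too high.

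Simulation takes the sharing into account: 3,000 trials, logit-normal clinic effects scaled to an ICC of about 0.05, uncorrected cluster-robust variance, normal reference, identical true effect in everyone. Disagreement was 0.222 for sex and 0.423 for age, with Monte Carlo standard errors √(0.222 × 0.778/3000) = 0.008 and √(0.423 × 0.577/3000) = 0.009. A second run of 4,000 trials gave 21% and 41%.

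**4. How far post-allocation membership could move a stratum estimate.** This uses illustrative assumptions only. Two equal prognostic halves have control suppression of 50% and 80% (mean 65%). The true RR is 0.81/0.65 = 1.246 in everyone. Stratum membership is 20% in both halves under control.
- The intervention lowers membership to 10% in the poorer half: risk in the stratum is 1.246 × (0.10 × 0.50 + 0.20 × 0.80)/0.30 = 0.872, so RR = 0.872/0.650 = 1.34.
- It lowers membership to 10% in the better half: 1.246 × (0.20 × 0.50 + 0.10 × 0.80)/0.30 = 0.748, so RR = 1.15.
- It does not affect membership: RR = 1.246, with no bias.

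**The case against.** The strongest reply is that the protocol defers analysis details to a SAP that is not shown, and that the reference to the same approach may mean only the GEE framework, into which an arm-by-subgroup term fits easily. That largely stands. The absence of a named interaction test or multiplicity rule is not itself an error here. A reader might infer that the protocol commits to re-running the model within each stratum and reading effects from stratum p-values. The text does not say so. What remains is that the approach as written is an arm contrast, and it does not answer the subgroup question until the term is added.

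A second reply is that the documents give no reason to think the intervention changes pregnancy or regimen. The added components are peer support, a video, two kinds of support group, and mental health screening with linkage; none is described as targeting either. This also stands. A reader might infer that biased subgroup estimates are likely, but the documents support only that they are possible. Nor do they fix regimen at T3: the word current comes from a data-item list, and the same row contains records from which an earlier regimen might be recovered.

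A third temptation is to cite the simulation under no effect, where at least one of the five age and sex strata was significant in about 27% of trials. Much of that is not caused by subgrouping. The overall test in the same setting rejected in about 10%, because the robust standard error is uncorrected with 12 clusters. With a small-sample variance correction and a t reference on 10 degrees of freedom, the two rates were 13.5% and 4.5%. The 27% should not be charged to this point.

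**Conclusion.** The point holds in limited form. The subgroup method as written does not test for differing effects, and one of the five factors, pregnancy, is defined by a post-allocation variable. Regimen timing is open, with the only listed source post-intervention.

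The size of the first part is about 22% disagreement on significance between the sexes and about 42% among the age groups when the effect is identical. This assumes equal strata, the protocol's planning values and an uncorrected robust variance. It matters only if stratum p-values are used to claim effect modification, which the protocol does not say it will do but does not guard against. The second part cannot be sized from the documents. The shift from 1.25 to 1.34 or 1.15 is an illustration that requires a 10-point effect on membership in one prognostic half, and it vanishes if membership is unaffected. The change is worth making before database closure; it is not a threat to the primary analysis.

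**What to change.** In the SAP:

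- For each subgroup factor, fit one GEE to all participants to whom the factor applies, with an arm-by-subgroup term. Report the ratio of risk ratios with its interval and interaction p-value. Give stratum risk ratios with intervals only, without p-values.
- Label these results exploratory. Five unadjusted interaction tests still carry up to 1 − 0.95⁵ = 22.6% chance of at least one false positive for a single outcome, taking them as independent.
- Define ART regimen and prior ART duration at the intervention start, using ART start dates and dispensing records. Put those who started ART later in a separate category. That category is itself formed after allocation, so describe it and do not interpret its arm contrast.
- Report pregnancy during the intervention descriptively by arm, not as an effect modifier.

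The cost is mainly wording, plus extracting a dated regimen from records already on the abstraction list. Interaction estimates will be imprecise with 12 clinics, which is an honest reflection of what the trial can show. Regimen at the start may be missing for some participants, because they are enrolled only at the 12-month assessment.
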